**Outcomes**

1. Primary outcome: the difference in 24-hour ambulatory systolic blood pressure change from baseline during the third trimesters of pregnancy;

2. Secondary outcomes: the difference in 24-hour ambulatory systolic blood pressure change from baseline during the second trimesters of pregnancy; the difference of daytime and nighttime ambulatory blood pressure, daytime and nighttime and 24-hour diastolic blood pressure, and clinic blood pressure changes from baseline;

3. Exploratory outcomes: incidence of preeclampsia; effect of exercise on blood pressure control in pregnant women with preeclampsia

4. Safety outcomes: activity tolerance decline rate; incidence of shortness of breath; incidence of heart failure;

5. Other relevant outcomes: severe complications of preeclampsia (eclampsia, heart failure, pulmonary edema, HELLP syndrome, DIC), fetal death, iatrogenic premature delivery, neonatal asphyxia, NICU. Compliance with oral aspirin and calcium; mobile phone exercise recording monitoring exercise intensity compliance; the Subjective Exertion Scale (RPE) monitors an individual's exercise intensity tolerance.

[figure not shown]

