**Data analysis**

The study is powered for the primary outcome measure of change in 24-hour ambulatory SBP from the first to the third trimester. The sample size calculation was based on the results of Lopes S et al.[14], who showed a decrease of -7.3 ± 12.7mmHg in 24-hour ambulatory SBP in the exercise group with 1.1 ± 8.2mmHg in the control group. A sample of 72 pregnant women (36 per group), with a two-sided significance level of 0.05, provided 90% statistical power to demonstrate this difference in 24-hour ambulatory SBP. In order to accommodate a 20% attrition rate, 90 pregnant women will be recruited (PASS11, independent t-tests; allocation ratio = 1).

Continuous variables will be presented as means ± standard deviations or median (interquartile range) according to normal distribution or not. Between-group differences at baseline will be tested with Student’s independent t-test or Mann–Whitney U test. For the categorical variables, results will be expressed as counts and percentages. Categorical variables will be tested with the chi-square test or Fischer test if appropriate between groups at baseline. The assessment of compliance with daily physical activity and safety will be summarized for the two groups. A cut-off of 80% of baseline physical activity during the second and third trimesters will be used to determine compliance well. Adverse events, if any, will be reported. The primary outcome and difference of the change in 24-hour ambulatory SBP from the first to the second trimester between groups will be analyzed using analysis of covariance, adjusting for baseline blood pressure. Other secondary outcomes will be analysis using general linear modelling to compare the difference of blood pressure change in the MPA and LPA groups at the second and third trimesters, adjusting for baseline blood pressure. The analyses will be conducted based on the intention-to-treat principle. The intention-to-treat population will comprise all the patients with the exception of those who do not complete ambulatory blood pressure measurement and physical activity monitoring at 3-time points for any reason, such as miscarriage, or preterm birth. Per-protocol set will be performed as a sensitivity analysis. Relative risks and 95% confidence intervals will also be provided. A two-sided p-value below 0.05 will be considered statistically significant in all analyses. Data will be analyzed using SPSS 25 statistical software.

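### Every p-value below 0.05 may be called statistically significant, although the study is powered for one outcome and lists about 8 to 15 secondary pressure comparisons

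*Supplement*

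**What the plan says.** All references are to the chronic hypertension protocol, the latest version in the supplement.

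- **Primary outcome** (Outcomes, item 1): one comparison. "Primary outcome: the difference in 24-hour ambulatory systolic blood pressure change from baseline during the third trimesters of pregnancy".
- **Secondary outcomes** (Outcomes, item 2): the second-trimester change in 24-hour systolic pressure, and then "the difference of daytime and nighttime ambulatory blood pressure, daytime and nighttime and 24-hour diastolic blood pressure, and clinic blood pressure changes from baseline".
- **Power** (Data analysis, first paragraph): the calculation is for the primary outcome, "with a two-sided significance level of 0.05, provided 90% statistical power".
- **Models** (Data analysis, second paragraph): analysis of covariance for the change in 24-hour systolic pressure in both trimesters. General linear models cover the remaining secondary outcomes at the second and third trimesters. All adjust for baseline pressure.
- **Significance rule** (end of the same paragraph): "A two-sided p-value below 0.05 will be considered statistically significant in all analyses".

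The protocol gives no hierarchy, gatekeeping rule or adjusted threshold, and does not say that secondary results are descriptive.

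**The concern.** The rule is an explicit decision, not a silence. It gives a night-time or clinic pressure result the same label as the one outcome for which the sample size was chosen. The secondary list holds many overlapping measures of the same thing, most of them at two time points, in a study planned around 72 evaluable women.

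The practical risk arises when the primary result is null. One of the other pressure measures may then fall below 0.05 by chance, and reporting it as a significant finding would comply with the plan. A reader who sees only that the analysis was prespecified could not tell such a result from a confirmed one.

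**Working it through.** **1. The plan's own figure.** Inputs from Data analysis: "a decrease of -7.3 ± 12.7mmHg in 24-hour ambulatory SBP in the exercise group with 1.1 ± 8.2mmHg in the control group"; "PASS11, independent t-tests; allocation ratio = 1".

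- Difference = 1.1 − (−7.3) = 8.4 mmHg.
- Root-mean-square SD = √((12.7² + 8.2²)/2) = 10.69.
- Two-sample t-test, two-sided 0.05, noncentral t: 36 per group gives power 0.908 and 35 per group gives just under 0.900. So 36 per group, 72 in all, reproduces.
- Attrition: 72/(1 − 0.20) = 90, as stated ("In order to accommodate a 20% attrition rate, 90 pregnant women will be recruited").

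The 0.05 level was therefore spent on one comparison, and for that comparison the error rate is 5%.

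**2. Count of secondary comparisons.** The list holds daytime and night-time systolic; daytime, night-time and 24-hour diastolic; and clinic pressure. The second-trimester 24-hour systolic change adds one.

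- Clinic pressure split into systolic and diastolic, each trimester tested separately: 7 × 2 + 1 = 15.
- Clinic pressure counted once, each trimester tested separately: 6 × 2 + 1 = 13.
- Clinic pressure split, one joint test per measure over both trimesters: 7 + 1 = 8.

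The text does not settle which applies. Counting clinic pressure once with joint tests would give 7 and barely moves the results. The per-protocol repeat and the exploratory outcomes are left out of the count.

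**3. Chance of at least one p < 0.05 when every null is true.** Under independence it is 1 − 0.95^m:

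- m = 15: 1 − 0.95^15 = 53.7%.
- m = 13: 1 − 0.95^13 = 48.7%.
- m = 8: 1 − 0.95^8 = 33.7%.

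For correlated tests I simulated equicorrelated two-sided z-tests (1,000,000 replicates). The common correlation is an assumption; the documents give none. The last two columns add the primary as one more test with the same correlation and keep only replicates in which it is not significant.

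| Assumed correlation | 15 tests | 8 tests | 15 tests, primary not significant | 8 tests, primary not significant |
|---|---|---|---|---|
| 0 | 54% | 34% | 54% | 34% |
| 0.5 | 36% | 25% | 34% | 23% |
| 0.7 | 26% | 19% | 23% | 16% |
| 0.8 | 20% | 16% | 16% | 12% |
| 0.9 | 14% | 12% | 10% | 8% |

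The two right-hand columns answer the question that matters most here: how often a null primary would be accompanied by a secondary result that the plan calls significant.

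**The case against.** The strongest reply is that the primary claim is already protected. There is one primary comparison, and the outcomes are sorted into numbered tiers with preeclampsia incidence labelled exploratory. Many statisticians do not adjust secondary p-values, and a general 0.05 level is a common convention. All of this stands, and it is why no multiplicity correction is asked for. What it does not answer is the label: the convention works when secondary results are presented as supportive, and this plan gives them the same word as the powered outcome.

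Four stronger readings are tempting and should not be drawn.

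- **That the trial's main conclusion has an inflated error rate.** It does not; the primary stays at 5%.
- **That a false claim is about as likely as not.** The 54% needs 15 independent tests. Day, night and 24-hour pressures come from the same recordings in the same women, and the 24-hour value contains the other two, so the upper end is implausible.
- **That safety outcomes are tested under the same rule.** Data analysis only says that safety will be summarised by group and adverse events reported. No safety test is specified. Relative risks, for their part, already come with 95% confidence intervals.
- **That the investigators intend to rescue a null primary with a secondary result.** Nothing in the documents says so. The point is what the rule permits.

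A further limit is that the groups are formed by measured early-pregnancy activity, not by randomisation (Grouping scheme, item 1). A difference can be misread as an effect of activity through confounding, whatever it is called, and this change does not address that.

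**Conclusion.** The point holds as a low-cost improvement. Followed as written, the plan permits significance claims on about 8 to 15 unpowered secondary comparisons with no control over the set. With all nulls true, the chance of at least one such claim is about 12% to 54% for 8 or 15 tests at a common correlation of 0 to 0.9. Given a non-significant primary it is about 8% to 23% at correlations of 0.7 to 0.9. These figures depend on the reading of the test count and on an equal-correlation assumption that the documents can neither confirm nor refute. Strongly correlated pressures make the lower part of each range the more credible, but every value exceeds the nominal 5%.

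**What to change.** Replace the closing significance rule in Data analysis with wording such as: *The two-sided 0.05 level for declaring statistical significance applies to the primary outcome, the change in 24-hour ambulatory systolic pressure from the first to the third trimester. Secondary and exploratory outcomes are reported as estimates with unadjusted 95% confidence intervals and interpreted as supportive or exploratory.*

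If a claim on a secondary outcome is wanted, name it in advance and test it in a prespecified order, only after a significant primary.

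The cost is a short change to the text, with none to data, sample size or models. The downside is that secondary results can no longer be headlined as significant.

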**Study quality control**

During the research process, regular inspection will be carried out to ensure that all contents of the research program are strictly complied with the protocol and that the filling of research data is correct and standardized.

1) Prior to the study, researchers should be trained and the recording methods and judgment standards should be unified. The training content includes but is not limited to research protocols, standard operating procedures involved in the study, study questionnaires and forms, informed consent, ethics, adverse event reports, knowledge of related diseases, and medical knowledge.

2) The researcher shall record all contents in the research form truthfully, and ensure the authenticity and reliability of the contents.

3) All observations in studies should be verified to ensure the reliability of data and ensure that all conclusions in clinical studies have corresponding original records. There are corresponding data management measures in the clinical research and data processing stage.

4) Periodically sample the case report form and check the original documents.

5) In order to ensure the safety of participants and ensure the accuracy, integrity and reliability of data, researchers should keep the original case observation table, clinical medical records and patients' visit records as the original records of this study. Researchers should be able to provide these original records upon request.

**Informed consent, ethical review and legal issues**

1. Informed Consent

The researchers should ensure that the enrolled pregnant women fully understand the nature of the study, the content of the study, the content of the examination, the duration of the study and data ownership, the possible risks and benefits, privacy protection, etc., and obtain written informed consent with the signed name and date. Ensure that patients have the opportunity to ask questions and time to consider the content of informed consent, and ensure that any questions patients may have during the study are answered promptly.

2. Ethical Review

The final study protocol, final written informed consent, and other relevant written information provided to patients must be approved and agreed upon in writing by the Ethics Committee prior to the initiation of studies. The investigator must ensure that these documents are submitted to the appropriate ethics committee and institute staff. The views of the Ethics committee must be expressed in writing.

3. Laws and Regulations

The implementation of this study is in accordance with the Declaration of Helsinki, the Technical Guidelines for Clinical Research on in vitro diagnostic reagents and the ethical principles of relevant laws and regulations on clinical trials of diagnostic reagents in China.

**Data preservation**

In order to ensure the evaluation and supervision of clinical studies by relevant national and responsible units, investigators should agree to keep all research-related data, including patient confirmation, original signed informed consent, detailed records of study forms, etc. The storage period is 3 years after the end of the study.

